### Strategies to improve adherence to interventions {11c}

During the consent procedure and the distribution of uniforms and DEET lotion, participants will be introduced to the importance of adherence. Containers of DEET lotion will be replaced every 2 weeks when the participants are tested for active malaria infection. Used containers will be weighed to calculate the average daily application. Since uniforms are worn every day at the camp and recruits are not allowed to wear any other outfit, adherence to uniform wearing is expected to be extremely high. Every 2 weeks, when participants are tested for active malaria infection, they will complete a questionnaire about activities that may affect malaria exposure, such as emergency home leave, and about adherence to uniforms and lotions. Participants who have left the camp during the 2 weeks before testing will be removed from follow-up for those 2 weeks.

### Relevant concomitant care permitted or prohibited during the trial {11d}

Participants are advised to refrain from self-prescription of any medication. All antimalarials will be dispensed to only participants with positive RDT.

### Provisions for post-trial care {30}

All recruits who will give their consent to participate will be insured for a period of 14 months (Fig. 1). The insurance will cover the 12 months of trial follow-up and 2 months after the trial ends on health issues that arise as a direct consequence of trial participation. During the trial, any participant who experiences a serious adverse event related to the study intervention will be transported to Bombo Regional Hospital. Referral to the regional hospital is to provide ancillary needs that may otherwise arise during trial participation.

**Fig. 1 Fig1:**
[figure not shown]
Schedule of events for the trial

The insurance will pay for ancillary care. This trial is considered to be of a minimum risk to participants and the form of compensation to be provided is treatment of participants who are harmed from trial-related incidents.

### Outcomes {12}

#### Primary outcome

The primary outcome is the incidence of *Plasmodium falciparum* infection as determined by active case detection through quantitative polymerase chain reaction (qPCR) in blood samples taken every 2 weeks and by passive case detection at the camp clinic in the case of illness. Personal travel by participants will be assessed every 2 weeks with brief questionnaires to estimate time away from the camp. Time at risk will exclude a 14-day period post-travel and a 14-day prophylactic period following any malaria treatment. Malaria infections will be detected by qPCR; this method detects malaria infections below the limit of detection (LOD) of rapid diagnostic tests (RDTs), although RDT will be used at the point of care for any participants symptomatic for malaria. We will perform the PlasQ qPCR assay as described previously [36]. This triplex TaqMan chemistry-based qPCR assay detects the pan-*Plasmodium* 18S rRNA sequence (PSpp18S) [37, 38] and the *P. falciparum*–specific acidic terminal sequence of the var genes (PfvarATS) [39]. The human RNaseP (HsRNaseP) gene serves as an internal control to evaluate the quality of DNA extraction and qPCR amplification. After finger-pricking by a study nurse, a blood sample of 200 μL of whole blood is drawn into an EDTA-containing collection tube (Greiner, MiniCollect®); 180 μL of the whole blood will be mixed with an equal volume of DNA/RNA Shield™ (Zymo Research, Irvine, CA, USA) and incubated at room temperature for 30 min before storage at –20 °C. On a weekly basis, samples will be packed with liquid nitrogen in a thermo-col container and transported under cold chain to the qPCR facility. A temperature long will be used on the storage at the field facility, during transport and at the qPCR facility. Upon arrival, DNA will be extracted from the samples using Quick-DNA™ MiniPrep kits (Zymo Research, Irvine, CA, USA), following the manufacturer’s guidelines. Amplification and qPCR measurements will be performed using the Bio-Rad CFX96 Real-Time PCR System (Bio-Rad Laboratories, Hercules, CA, USA). All qPCR runs will be performed with a no-template control (NTC) and with *P. falciparum* NF54 DNA as a positive control.

### Participant timeline {13}

#### Sample size {14}

The sample size calculations are based on the comparison of the incidence of malaria infection between the trial arms. The primary comparison is between ETU + DEET and PTU + DEET. An expected total of 1500 recruits per year form combania with a mean of 40 recruits each. We expect roughly 37 combania available for randomisation. A combania is a military subsection of recruits who carry out all activities together and sleep in the same dormitory. The dormitories can accommodate 30 to 50 recruits. The trial is randomised by combania because of the risk of contamination between recruits in the same company if the trial were individually randomised and because it is expected that a whole company will use the same interventions in practice in a “real world” use scenario.

The outcome is the incidence of malaria infection determined by PCR every 2 weeks. As a baseline estimate (with neither treated uniform nor repellent), the most recent available incidence of malaria infection in Mgambo camp among recruits is 0.68 per person per year in 2015 [40].

The sample size was estimated using a simulation of 1000 trials using generalized linear mixed effects models written in R statistical software version to estimate the power and the precision of the estimated incidence rate ratio (IRR) (the precision is measured here by the expected width of the confidence interval). We assumed a Poisson distribution for the incidence of malaria infections among recruits and a lognormal distribution of the combania cluster effects.

An assumed efficacy of 50% for PTU + DEET with a compliance of 80% would lead to an incidence rate of 0.41 infections per person per year. An assumed efficacy of 70% for ETU + DEET and compliance of 80% would lead to an incidence rate of 0.27 and an IRR of 0.66. With 12 clusters each of 40 recruits and 12 months of follow-up, we would have 89% power to detect this difference as significant and be able to estimate the IRR with a confidence interval of 0.49 to 0.88. After exploring different scenarios for unequal cluster randomisation to maximise power, we will randomise 12 combania (about 480 participants) for each arm of the primary comparison (PTU + DEET vs. ETU + DEET) and 6 combania (about 240 participants) to each of PTU + placebo lotion and untreated uniform + placebo lotion.

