While there is very strong evidence that repellents and treated clothing are effective in reducing bites from biting arthropods [17], a recent systematic review found no evidence that topical repellents prevent malaria, insufficient evidence that spatial repellents prevent malaria and limited evidence that permethrin-treated clothing prevents malaria [18]. Two randomised control trials (RCTs) were included in the review; the evidence from them was deemed to be of low certainty due to the size and conduct of the studies. These studies were conducted in specific populations in Colombia (military personnel) and Pakistan (Afghan refugees). Insecticide-treated clothing may have a protective effect against clinical malaria caused by *Plasmodium falciparum* (risk ratio 0.49; *95% CI* (0.29–0.83)) and *P. vivax* (risk ratio 0.64; *95% C*I (0.40–1.01)) [18]. Therefore, World Health Organization (WHO) guidelines do not recommend insecticide-treated clothing for day-to-day use by the general population, although it may be beneficial as an intervention to provide personal protection against malaria in specific population groups [19].

In the case of military uniforms, the surface area of skin protected by DEET is small compared to that protected by clothing, limited to the hands, neck and face, and it is likely that the additional DEET provides only minimal additional protection. Furthermore, daily compliance with repellents as required for optimal disease prevention is rarely met, even for short periods of time [20]. It is therefore useful to estimate the protection provided by DEET in addition to treated uniforms to evaluate its utility and cost-effectiveness.

This study will evaluate the effectiveness on the incidence of malaria infection detected by polymerase chain reaction (PCR) of permethrin-treated and etofenprox-treated uniforms alone and in combination with DEET. We will also evaluate adherence to the interventions.

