### Objectives {7}

#### Primary objective

To estimate the effect of etofenprox- compared to permethrin-treated uniforms by comparing etofenprox-treated uniforms (ETUs) plus DEET lotion compared to permethrin-treated uniforms (PTUs) plus DEET lotion on the incidence of *Plasmodium falciparum* malaria confirmed by polymerase chain reaction (PCR)

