#### Defining compliance

Compliance with the intervention will be estimated as the proportion of 2-week time intervals where the participant was compliant and estimated by study arm and over time. The JKT recruits must wear uniforms and will be provided with two treated uniforms. They have no alternative clothing, leading to an expected 100% compliance; compliance with clothing will not be monitored. Participants’ repellent bottles will be weighed twice weekly to estimate application rates. If a bottle contains more than 50% of the required dose, the participant will be recorded as non-compliant.

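### The sizing's single 80% compliance figure conflicts with the 100% uniform wear the plan expects, and the stated 0.27, IRR 0.66 and 89% power fit neither assumption

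*Protocol article*

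**What the plan says.** The primary objective concerns the fabric treatment, studied with the same lotion in both arms: "To estimate the effect of etofenprox- compared to permethrin-treated uniforms by comparing etofenprox-treated uniforms (ETUs) plus DEET lotion" against permethrin-treated uniforms plus DEET.

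Sample size {14} starts from an untreated rate: "the most recent available incidence of malaria infection in Mgambo camp among recruits is 0.68 per person per year in 2015". It then gives the comparator arm, "An assumed efficacy of 50% for PTU + DEET with a compliance of 80% would lead to an incidence rate of 0.41", and the candidate arm, "An assumed efficacy of 70% for ETU + DEET and compliance of 80% would lead to an incidence rate of 0.27 and an IRR of 0.66". For 12 combania of 40 per primary arm, followed for one year, it claims 89% power and an interval of 0.49 to 0.88. It does not say whether the 80% refers to the uniform, the lotion or both.

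Elsewhere the plan treats the two components differently. On uniforms, Defining compliance says: "They have no alternative clothing, leading to an expected 100% compliance; compliance with clothing will not be monitored". Section {11c} says that "adherence to uniform wearing is expected to be extremely high". Defining compliance records non-compliance from the weight of the lotion bottle alone. On what the lotion contributes, Background {6a} says that "it is likely that the additional DEET provides only minimal additional protection".

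**The concern.** Multiplying a system's full efficacy by 80% treats the other 20% of time as wholly unprotected, as if the treated uniform were off. On the plan's own description, a recruit who skips the lotion is still in the treated uniform, which is the component under test. Missed lotion is a lapse in a background treatment that both primary arms share, so it should dilute the contrast between arms only a little.

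The choice matters because the planned IRR, power and interval depend heavily on it. The stated candidate rate also fails to follow from its own inputs, so a reader cannot tell which compliance assumption the 89% represents. If the arithmetic alone is corrected, the trial looks short of power. If the compliance input is also moved to where Defining compliance puts it, the trial looks comfortably powered. The published power cannot be repaired until the assumption is settled.

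**Working it through.** **Inputs from Sample size {14}:** untreated rate 0.68 per person-year; efficacies 50% and 70%; compliance 80%; 12 combania × 40 recruits × 1 year = 480 person-years per primary arm; Poisson counts with lognormal combania effects.

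**Assumed, because not stated there:** two-sided 5% test; between-combania log-SD σ, shown over a range; 50% and 70% read as efficacies under full use of both components.

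**1. The plan's own rates.** Rate = 0.68 × (1 − efficacy × compliance).

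- PTU + DEET: 0.68 × (1 − 0.5 × 0.8) = 0.408. The stated 0.41 is reproduced.
- ETU + DEET: 0.68 × (1 − 0.7 × 0.8) = 0.299. The stated 0.27 is not reproduced.
- IRR from the stated inputs: 0.299 / 0.408 = 0.73. The stated 0.66 is simply 0.27 / 0.41.
- A rate of 0.27 would need about 75% efficacy at 80% compliance (0.68 × 0.40 = 0.272), or 70% efficacy at about 86% compliance.

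**2. Uniforms at 100%, lotion at 80%.**

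- *Negligible DEET share:* 0.68 × 0.50 = 0.34 and 0.68 × 0.30 = 0.204; IRR 0.60.
- *Multiplicative effects, DEET efficacy d:* each full-use rate is multiplied by (1 − 0.8d)/(1 − d). The factor is the same in both arms, so the IRR stays at 0.30/0.50 = 0.60. For d = 0 to 0.3 the rates are 0.34 to 0.37 and 0.20 to 0.22.
- *Additive effects, DEET share d:* IRR = (0.30 + 0.2d)/(0.50 + 0.2d). At d = 0.1 this is 0.32/0.52 = 0.62. At d = 0.3 it is 0.36/0.56 = 0.64, with rates 0.68 × 0.56 = 0.38 and 0.68 × 0.36 = 0.24.

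**3. Power.** Var(log IRR) = 1/(480·r₁) + 1/(480·r₂) + 2σ²/12; power = Φ(|log IRR|/SE − 1.96).

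Worked example at σ = 0.15 for 0.408 and 0.299: expected events 195.8 and 143.6; SE = √(1/195.8 + 1/143.6 + 2 × 0.0225/12) = 0.126; |log 0.733|/SE = 0.310/0.126 = 2.47; power = Φ(0.51) = 69%.

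| Case | Rates | IRR | σ = 0 | σ = 0.15 | σ = 0.20 | σ = 0.25 |
|---|---|---|---|---|---|---|
| As stated | 0.41 / 0.27 | 0.66 | 96% | 90% | 85% | 78% |
| 80% on whole system, arithmetic corrected | 0.408 / 0.299 | 0.73 | 81% | 69% | 62% | 54% |
| Uniform 100%, negligible DEET share | 0.34 / 0.204 | 0.60 | 98% | 95% | 92% | 88% |
| Uniform 100%, additive DEET share 0.3 | 0.381 / 0.245 | 0.64 | 96% | 91% | 87% | 81% |

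A mixed-model simulation (400 trials per case) at σ = 0.15 gave 91%, 71% and 94% for the first three rows, in line with the formula.

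**4. Which σ?** At the stated rates, 89% power needs σ of about 0.16. The stated interval of 0.49 to 0.88 implies σ of about 0.24, where power at those rates is about 80%. The document does not settle σ, so power can only be given as a range.

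**The case against.** The strongest reply is that diluting a planned effect for imperfect compliance is ordinary prudence, and that this stands on the safe side. It does. Compared with 80% on the whole system, component-specific compliance moves the IRR further from 1 and raises power, despite fewer events.

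Nor is full exposure to treated fabric guaranteed. Section {11c} calls uniform adherence extremely high, not complete, and plans a fortnightly questionnaire that covers uniforms. The unblinding procedure moves a recruit with a severe, possibly related event to untreated uniforms and keeps that time in the intention-to-treat analysis. A single system-level allowance is a defensible simplification.

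One component-specific split does come close to the stated rates. With additive effects and a DEET share of 0.5, they are 0.68 × 0.60 = 0.408 and 0.68 × 0.40 = 0.272. It would leave the permethrin uniform with no effect of its own, against the view in Background {6a} that DEET adds little, so it does not rescue the figures.

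Three stronger readings are tempting, and the documents do not support them:

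- *That the trial is sized for the wrong comparison, or that the 12:12:6:6 allocation would change.* The allowance is conservative, and nothing in the protocol shows that a different compliance input would alter the allocation.
- *That the IRR is exactly 0.60.* That needs multiplicative effects or a negligible DEET share; additive shares of 0.1 to 0.3 give 0.62 to 0.64.
- *That compliance alone explains the gap between the stated power and about 95%.* The rise from 90% to 95% at σ = 0.15 nets two changes: correcting the 0.27 (90% to 69%), then changing the compliance input (69% to 95%).

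**Conclusion.** The contradiction between Sample size {14} and Defining compliance is real. The 80% allowance itself is acceptable as a planning choice and does not invalidate the number of combania. What does not stand is the set of stated figures: 0.27, IRR 0.66 and 89% power follow neither from 80% on the whole system nor from full uniform wear with a small to moderate DEET share.

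On the stated inputs the power claim is too high: about 69% at σ = 0.15, 54% at σ = 0.25, and no more than about 81% without clustering. With full uniform wear and a negligible DEET share it is about 95% and 88% at the same two σ values; an additive DEET share of 0.3 lowers these to 91% and 81%.

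These results rest on a two-sided 5% test, an assumed σ, full-use efficacies of 50% and 70%, and an assumed form for combining uniform and DEET effects. The failure of 0.27 to follow from 0.68, 70% and 80% under the calculation that reproduces 0.41 needs none of the power assumptions.

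**What to change.** In Sample size {14}, state which component the 80% covers and reconcile it with Defining compliance. If less than full uniform wear is really expected, correct the 100% statement there instead.

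Rerun the existing simulation and report rates, IRR, power and expected interval for two labelled cases:

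1. 80% on the whole system, kept as the conservative case, with the ETU + DEET rate corrected.
2. Component-specific compliance: uniforms as Defining compliance expects, 80% on the lotion only.

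State the between-combania SD and how uniform and DEET effects are assumed to combine. Do not let the second case replace the first: it depends on uniform wear that Defining compliance says will go unmonitored.

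The cost is one simulation rerun and a few sentences. The price is that the conservative case may openly show power below 89%, which the sponsor would have to acknowledge. No change in the number of combania or in the allocation is proposed.

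### Sample size: 70% efficacy, 80% compliance, a rate of 0.27 and an IRR of 0.66 for ETU + DEET cannot all hold, so the 89% power is not tied to the declared assumptions

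*Protocol article*

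**What the plan says.** All the figures are in the protocol article, Sample size {14}. The baseline, with neither treated uniform nor repellent, is given as "the most recent available incidence of malaria infection in Mgambo camp among recruits is 0.68 per person per year in 2015". Two planning rates follow in consecutive sentences:

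- PTU + DEET: "An assumed efficacy of 50% for PTU + DEET with a compliance of 80% would lead to an incidence rate of 0.41" per person-year.
- ETU + DEET: "efficacy of 70% for ETU + DEET and compliance of 80% would lead to an incidence rate of 0.27 and an IRR of 0.66".

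For a primary comparison of 12 combania per arm, 40 recruits in each and a year of follow-up, the article then claims "89% power to detect this difference as significant and be able to estimate the IRR with a confidence interval of 0.49 to 0.88". The calculation is described as a simulation of 1000 trials with Poisson counts and lognormal combania effects. The size of the combania effect, the alpha and the sidedness of the test are not given there. The section Estimates of protective efficacy plans 95% confidence intervals. ETU + DEET against PTU + DEET is the primary objective.

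**The concern.** Both rates are presented as the result of the same three quantities: baseline, efficacy and compliance. One follows from them and the other does not. The IRR of 0.66 inherits the discrepancy, and the 89% power and the interval are both stated for that difference. If the declared 70% is what the investigators believe, the primary comparison is aimed at a smaller effect than the one that was powered. A null result would then be read as coming from a trial with an 11% chance of missing the assumed difference, when that chance would be roughly 31-45%. If only the efficacy label is wrong, readers are told that the trial can detect a less optimistic efficacy than it was planned for.

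**Working it through.** **Inputs.** From Sample size {14}: baseline 0.68; efficacy 50% and 70%; compliance 80%; 12 combania of 40 per primary arm for 12 months, so 12 x 40 x 1 = 480 person-years per arm. Two assumptions are mine. The test is taken as two-sided at 5%, in line with the planned 95% intervals. The between-combania SD on the log scale is back-solved from the article's own figures.

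**1. Rates.** Rate = 0.68 x (1 - efficacy x compliance).

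- PTU + DEET: 0.68 x (1 - 0.50 x 0.80) = 0.68 x 0.60 = 0.408. The stated 0.41 is reproduced.
- ETU + DEET: 0.68 x (1 - 0.70 x 0.80) = 0.68 x 0.44 = 0.299. The stated 0.27 is not reproduced.
- IRR: 0.44 / 0.60 = 0.73. The baseline cancels.

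Rounding does not explain the gap: a baseline of 0.675 to 0.685 gives 0.297 to 0.301. A rate of 0.27 needs efficacy of (1 - 0.27/0.68) / 0.80 = 75%. Then 0.68 x 0.40 = 0.272, and 0.27/0.41 = 0.66.

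Two other readings also fail to give the stated pair:

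- Full compliance gives 0.34 and 0.20.
- Compliance as an exponent gives 0.68 x 0.5^0.8 = 0.39 and 0.68 x 0.3^0.8 = 0.26. Their ratio is 0.66, but neither rate matches.

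**2. Between-combania SD.** SE² = 1/(480 r1) + 1/(480 r2) + 2 SD²/12. At 0.41 and 0.27 the Poisson part is 1/196.8 + 1/129.6 = 0.01280.

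- From 89% power at an IRR of 0.66: SE = 0.4155 / (1.960 + 1.227) = 0.130, so SD = √(6 x (0.01700 - 0.01280)) = 0.16.
- From the interval: SE = ln(0.88/0.49) / 3.92 = 0.149, so SD = √(6 x (0.02231 - 0.01280)) = 0.24.

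**3. Power if 70% stands.** At 0.408 and 0.2992 the Poisson part is 1/195.84 + 1/143.62 = 0.01207, and |ln 0.733| = 0.310. Power = Φ(0.310/SE - 1.96).

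| SD | SE | Power (formula) | Expected 95% CI |
|---|---|---|---|
| 0 (no clustering) | 0.110 | 81% | not needed |
| 0.16 (from 89%) | 0.128 | 68% | 0.57 to 0.94 |
| 0.24 (from the interval) | 0.147 | 56% | 0.55 to 0.98 |

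Simulating a Poisson model with lognormal combania effects gives 69% at SD 0.16, 65-67% at 0.18-0.19, 60% at 0.24 and 55-57% at 0.26-0.27. Formula and simulation together give about 55-69%.

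**4. Stated interval against stated power, both at an IRR of 0.66.**

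- Two-sided 5%: Φ(0.4155/0.149 - 1.96) = 79%, or 80% using 0.27/0.41 unrounded. Rounding of the limits gives 77-82%.
- One-sided 5%: Φ(0.4155/0.149 - 1.645) = 87%.
- At two-sided 5%, 89% power would go with an interval of 0.66 x exp(±1.96 x 0.130), about 0.51 to 0.85.

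**The case against.** The strongest reply is that only the efficacy label is wrong. Under 75% efficacy the rate and the IRR agree with each other. The stated interval is also centred on √(0.49 x 0.88) = 0.66, which suggests that the simulation was run at 0.66. The 89% could then be a sound result for that effect. This stands. A reader might infer that the IRR is 0.73 and that the trial is underpowered; the article supports that only if 70% is the intended assumption. The slip could even lie elsewhere: with compliance as an exponent, a baseline of about 0.71 would return both rates (0.71 x 0.574 = 0.41; 0.71 x 0.382 = 0.27), but the stated baseline is 0.68. In every case some stated input is wrong or unexplained.

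A reader might also infer that the interval flatly contradicts the 89%. That needs a two-sided 5% test. It is the natural reading beside planned 95% intervals, but neither alpha nor sidedness is stated for the power, and one-sided 5% comes within two points. Even then, if 70% stands, one-sided power at SD 0.24 is Φ(0.310/0.147 - 1.645) = 68%.

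Finally, a reader might expect the excluded travel, leave and post-treatment time to lower power further. The article gives no figure for that loss. Recruitment {15} and the retention section {18b} provide for enrolling new recruits who join a trial combania, which works the other way. No claim is made on this.

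**Conclusion.** The inconsistency among efficacy, compliance, rate and IRR is certain and rests on no outside assumption. Its consequence for power is conditional. If 70% efficacy is intended, the planned IRR is 0.73 and two-sided 5% power is about 55-69%, given a between-combania SD back-solved from the article's own power or interval; without any clustering it is at most 81%. If 75% was intended, 0.27 and 0.66 stand and the efficacy figure is the error. The mismatch between interval and power (79-80% against 89%) is a secondary point that holds only for a two-sided 5% test. Neither the estimand, the analysis nor the allocation is in question here.

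**What to change.** In Sample size {14}, reconcile efficacy, rate and IRR for ETU + DEET: either keep 70% and restate the rate as 0.30 and the IRR as 0.73, or state the efficacy, with its formula, that yields 0.27 and 0.66. Rerun the existing simulation at the declared assumptions. Report power and expected confidence interval from that single run, with the between-combania SD, alpha and sidedness.

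The cost is one rerun and one amended paragraph, and the stated power may become less favourable. No change in sample size is requested; the design already uses 12 + 12 + 6 + 6 = 36 of roughly 37 expected combania. The Trial status section says that recruitment has not begun, so the correction can be made before any data exist.
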